### Randomisation and blinding

Following baseline testing, participants will be randomised to one of three 12-week interventions; HIIT, SSE or Con (details of the three treatment arms in Table 1). An independent biostatistician will randomise subjects by a simple randomisation procedure using computerised sequence generation with an allocation ratio of 1:1:1. Two tables based on BMI (< 35 kg.m^2^ or > 35 kg.m^2^) will be created. As exercise interventions cannot be blinded from participants and staff (accredited exercise physiologists) implementing the intervention, only staff undertaking sample analysis and endpoint data processing will be blinded to group allocation.

**Table 1 Tab1:** Details of the three treatment arms

Intervention	Details
Con	Standard care consisting of basic exercise advice (150 min/week) with no supervised or structured exercise. We do not anticipate the control group will engage in a significant amount of exercise compared to their baseline physical activity levels without the addition of a structured exercise program [11]
SSE group	Minimum physical activity recommendations (150 min per week) [40], in three supervised 50-min sessions/week of continuous moderate intensity exercise sessions of cycling at 50–60% HRR (~ 3.5 METs)
HIIT group	Minimum vigorous physical activity recommendations (~ 75 min per week) [40], in three supervised sessions/week of HIIT exercise (cycling/running). Based on existing literature, pilot data [43] and patient consultation, we will use a practical weekly training program encompassing two successful HIIT protocols [16, 17, 55]: two sessions/week of short constant load cycling of 12 × 1 min at > 85% HRR (> 9 METs; [1 min HIIT]) with 1 min active recovery; one session/week of cycling 6–8 × 4 min at > 85% HRR (> 9 METS; [4 min HIIT]) with 2 min active recovery

*Con* control- standard care, *SSE* supervised standard exercise, *HIIT* high-intensity intermittent training, *min* minutes, *MET* metabolic equivalent task, *HRR* heart rate reserve

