### Outcome measurements

Outcome measures will be taken pre-intervention and post-intervention (Fig. 1). The primary outcome is the change in insulin sensitivity (measured by the steady state glucose infusion rate determined during the hyperinsulinemic-euglycemic clamp) between the three interventions. Secondary outcomes include reproductive health via hormone profiles (AMH and steroid profiles), mental health and health-related quality of life, body composition, physical activity behaviours and cardio-respiratory fitness.

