### Statistical methods and determination of sample size

Primary analyses will be undertaken on an intention-to-treat basis, including all participants as randomised, regardless of treatment actually received. The HIIT group will be compared with the SSE and Con groups using a planned contrast of change from baseline to the week 12 endpoint on the basis of insulin sensitivity scores using a mixed-model repeated measures analysis. Stratification variables will be evaluated and retained in analyses where they are measured as significant or quasi-significant. Transformation of scores, including categorisation, may be undertaken to meet distributional assumptions and accommodate outliers. Comparisons of changes in insulin sensitivity scores from baseline to other time points will be undertaken as secondary analyses. Data will be analysed by SPSS and significance will be accepted when *p* < 0.05. Where required *p* values from the statistical analysis will be adjusted for multiple comparisons using the false discovery rate [49] and statistical significance will be accepted when false discovery rate q < 0.1.

Using the primary outcome of change in insulin sensitivity (as measured by the glucose infusion rate) of 27 mg/min/m^2^ (effect size (Cohens d) = 0.25) in response to training [4], we require a total of 42 participants or *n* = 14 per group to achieve a power of 85% (α = 0.05). With an approximate attrition rate of 30% based on previous research, we will recruit 60 participants [4, 12].

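### The stated 85% power with 14 women per arm does not hold for the planned HIIT contrasts: at d = 0.25 on the SD of change, pairwise power is about 10%

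*Protocol article*

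**What the plan says.** All the sizing inputs are in one paragraph of the protocol article, under Statistical methods and determination of sample size.

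- Effect: a "change in insulin sensitivity (as measured by the glucose infusion rate) of 27 mg/min/m^2", described as "effect size (Cohens d) = 0.25) in response to training [4" (the bracketed number is a literature reference).
- Size and power: "in response to training [4], we require a total of 42 participants", that is "14 per group to achieve a power of 85% (α = 0.05".
- Attrition: about 30%, giving 60 women to recruit.

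The paragraph before it fixes the primary analysis: "The HIIT group will be compared with the SSE and Con groups using a planned contrast of change from baseline" to week 12, in a mixed model for repeated measures. Outcome measurements defines the primary outcome as the "change in insulin sensitivity (measured by the steady state glucose infusion rate determined during the hyperinsulinemic-euglycemic clamp) between the three interventions". Randomisation and blinding sets "computerised sequence generation with an allocation ratio of 1:1:1".

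The article gives no SD, no pre-post correlation, no sidedness and no name for the test used in sizing.

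**The concern.** A standardised difference of 0.25 is small, and 14 per arm is a small group. For a comparison of two arms, those figures do not normally go with 85% power.

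There is a second mismatch. The effect is described as what training does to a woman's own value, which is a pre-post change. The primary question is how much more insulin sensitivity changes under HIIT than under SSE or standard care. A pre-post response to training cannot be taken as the difference between two supervised exercise arms that are matched for training volume.

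What is at stake is how the result is read. A reader who meets a non-significant HIIT versus SSE contrast beside a published 85% power claim will give the null more weight than the design supports.

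**Working it through.** **Inputs.** From the article: d = 0.25; raw change 27 mg/min/m²; n = 14 per arm, N = 42; α = 0.05; stated power 85%; attrition 30%. Assumed, because not stated: two-sided testing and the pre-post correlation ρ (a range is shown).

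**Attrition step.** 42 / (1 − 0.30) = 60. This reproduces and is not in question.

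**Planned contrast, d on the SD of change.** The noncentrality is δ = d / √(1/n₁ + 1/n₂), with power from the noncentral t distribution.

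- HIIT v SSE, or HIIT v Con: δ = 0.25 / √(2/14) = 0.661. Power is 9.8% with 26 df and 9.9% with 39 pooled df.
- HIIT v the average of the other two arms: δ = 0.25 / √(1/14 + 1/28) = 0.764. Power is 11.6%.
- One-sided, the pairwise figure is 15.9%.
- All 60 women retained (20 per arm): 12.0%.
- Size needed for 85%: 289 per arm by the t test, 288 by the normal approximation.

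**Planned contrast, d on the raw SD.** The SD of change is then √(2(1 − ρ)) raw SDs, so the effect on the change scale is 0.25 / √(2(1 − ρ)). Pairwise, two-sided, 39 df:

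| ρ | effect in SD of change | power |
|---|---|---|
| 0.5 | 0.25 | 9.9% |
| 0.8 | 0.40 | 17.5% |
| 0.9 | 0.56 | 30.3% |
| 0.95 | 0.79 | 53.2% |
| about 0.98 | about 1.16 | 85% |

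Adjusting for baseline instead of analysing change gives 18.9%, 31.6% and 54.2% at 0.8, 0.9 and 0.95, so the choice of model makes little difference.

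**Where 85% can come from.** For the omnibus group-by-time test (3 arms × 2 times), λ = f² × N × 2 / (1 − ρ), with 2 and 39 df.

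- 0.25 read as Cohen's f, ρ = 0.5: λ = 0.0625 × 42 × 2 / 0.5 = 10.5, power 80.3%. At ρ = 0.55 power is 84.5%, and it reaches 85% at ρ of about 0.556. With ρ held at 0.5, N = 48 gives 86.0%.
- f = d/2 = 0.125: power is 26.7% at ρ = 0.5 and 59.0% at 0.8. It reaches 85% at ρ of about 0.89.
- Paired pre-post test pooling all 42 women: 35.3% with d on the SD of change. With d on the raw SD it reaches 85% at ρ of about 0.86.

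None of these is the planned contrast of HIIT with SSE and Con.

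**What 14 completers per arm can detect.** 85% power for a pairwise contrast needs d = 1.18 (26 df) or 1.16 (39 df), about 1.2 SD of change. The stated figures imply an SD of 27 / 0.25 = 108 mg/min/m². If that is the SD of change, the detectable difference is 1.16 × 108 ≈ 125 to 1.18 × 108 ≈ 127 mg/min/m², about 4.7 times the stated 27. If 108 is the raw SD, the detectable difference is smaller wherever ρ exceeds 0.5.

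**The case against.** The strongest defence is that the article is condensed and its calculation may be sound on inputs it does not print. A reader might infer from the figures above that 85% is unreachable with d = 0.25 on any reading. That goes too far. With d on the raw SD, both the pooled pre-post test (ρ about 0.86) and the group-by-time interaction with f = 0.125 (ρ about 0.89) reach it. Whether such correlations are realistic for the clamp measure cannot be judged from the article.

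A reader might also infer that 42 is simply the answer for 80% power and that 85% needs 48. That holds only at an assumed ρ of 0.5. At about 0.556, 42 women do give 85% on the f reading. In that case the 85% would be right for the omnibus test, and the faults would be the label d and the use of an omnibus test to size a contrast. A d-for-f mix-up is a likely explanation, but the document does not establish it.

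Two further inferences are too strong. The first is that the trial has a one-in-ten chance of finding a HIIT benefit. The 10% applies only if the true between-arm difference equals 0.25 SD of change, and the article never states a between-arm difference. The second is that the investigators would present a null as equivalence. The protocol makes no equivalence claim, and its Discussion says the trial should inform larger ones.

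What stands after all this is that every route to 85% leads to a test that is not the primary analysis, or needs a correlation near 0.98 for the one that is.

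**Conclusion.** The power statement is not supported for the analysis it is meant to justify. For the planned pairwise contrasts with 14 women per arm, power is about 10% if d = 0.25 is on the SD of change, or on the raw SD with ρ = 0.5. It is about 12% for HIIT against the average of the other two arms. On the raw SD, pairwise power rises to 53% at ρ = 0.95, still well short of the claim. Separately, the effect used is a pre-post training response while the primary outcome is a comparison between arms, so even a correctly computed figure would answer a different question.

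These results assume two-sided α = 0.05, equal arms and 14 completers in each. That 85% fails for the planned contrast is firm for any correlation below about 0.97. The exact power is conditional on the unstated SD basis and correlation.

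**What to change.** Keep 60 women and rewrite the sample-size paragraph to:

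1. state whether 0.25 is Cohen's d or f, which SD standardises it, the pre-post correlation, and the test used for sizing;
2. say that 27 mg/min/m² is a pre-post response to training, and state separately what between-arm difference is assumed, if any;
3. replace the 85% with the power of the planned HIIT v SSE and HIIT v Con contrasts, computed from the sponsor's own inputs (about 10% if d = 0.25 is on the SD of change). An omnibus figure may stand beside it if labelled as such, with its correlation; the 80% at ρ = 0.5 should not be copied in as a substitute;
4. give the pairwise difference that 14 completers per arm can detect with 85% power, about 1.2 SD of change, and in mg/min/m² once the SD is known.

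The cost is wording only, with no added participants. The downside is that the stated power becomes less favourable.

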## Discussion

PCOS is under-recognised by health professionals and leaves women on track for a plethora of chronic conditions ranging from anxiety and depression to diabetes, subfertility, cardiovascular disease and stroke [1, 50–52]. Despite affecting around one million Australian women and costing over $800 million nationally each year [10, 53, 54], there are no optimal treatments.

Overall, HIIT in PCOS promises greater metabolic benefits with demonstrated acceptability and safety [23]. It has the potential to address general and PCOS-specific barriers (low confidence and physical limitations) to standard exercise participation [14, 15]. However, evidence from prospective studies comparing volume-matched HIIT and standard moderate exercise for efficacy and enjoyment is lacking in women generally and more importantly in women at high risk of metabolic disease (i.e. PCOS).

Here, we describe the protocol of a study evaluating the effectiveness and mechanistic impacts of a practical allied health supervised 12-week HIIT or moderate intensity exercise program on cardiometabolic, reproductive and mental health in overweight women with PCOS. This trial aims to demonstrate comparative efficacy of different exercise protocols to inform vital large-scale clinical trials and ultimately best clinical practice in treatment of PCOS. It will advance the understanding of PCOS management by providing insights into the best exercise intensities to improve insulin sensitivity. Further helping to address the limitations highlighted by the recently released international guidelines in PCOS lifestyle management [9]. Finally, we will explore the impact of different exercise protocols on reproductive health (anti-müllerian hormone and steroid profiles), mental health and health-related quality of life and molecular mechanisms that affect insulin resistance. The impact of this work is likely to be significant due to the unprecedented public health challenge of PCOS in young Australian women for which we currently have no optimal treatment.

## Abbreviations

AMH: Anti-müllerian hormone
BMI: Body mass index
Con: Standard care
DASS: Depression Anxiety Stress Scale
DXA: Dual energy x-ray absorptiometry
ECG: Electrocardiogram
GXT: Graded exercise test
HIIT: High intensity intermittent training
HRR: Heart rate reserve
Insulin clamp: Hyperinsulinemic-euglycemic clamp
IPAQ: International Physical Activity Questionnaire
METs: Metabolic equivalent task
PBMC: Peripheral blood mononuclear cell
PCOS: Polycystic ovary syndrome
RCT: Randomised controlled trial
SSE: Standard supervised exercise (moderate intensity exercise)
TGFβ1/3: Transforming growth factor beta 1/3
